### Mediator analysis

Potential mediation will be explored using a simple product-of-coefficient approach using Sobel tests [50]. This test will examine whether the ‘indirect effect’ (or the ‘mediated effect’) of the MobileMums intervention is significantly different from zero [50]. The indirect effect is the difference between the ‘total effect’ of the intervention on physical activity and the ‘direct effect’ of the intervention on physical activity after controlling for proposed mediators (Social Cognitive Theory constructs). It should be acknowledged that this trial was not powered to detect mediation and this will be an exploratory analysis.

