### Theoretical mediators

The MobileMums program is grounded in Social Cognitive Theory and the intervention strategies target change in the specific theoretical constructs proposed [25], therefore the following five constructs are being evaluated as potential mediators via the self-administered questionnaire at each data collection point. *Physical activity barrier self efficacy* is assessed on a 5-point Likert scale (from 1 ‘not at all confident’ to 5 ‘very confident’), using a 12-item tool adapted from a previous scale [39]. Our version includes two additional items for postnatal women (i.e., I could exercise even when: ‘I don’t have anyone to look after the kids’; ‘I have housework to do’). This adapted version of the scale has demonstrated sensitivity to change among postnatal women [10,26] and had acceptable internal consistency (Cronbachs α = 0.71) [26]. *Outcome Expectancy* is measured using 10-item scale developed by Rodgers & Brawley [40]. Participants rate outcome likelihood (on a 10-point scale, 0–100% likelihood) and outcome value (on a 9-point scale, 1–9 importance) for seven physical activity outcomes and ratings are multiplied to indicate overall outcome expectancy (range 0–900). Consistent with the creator’s recommendations, the specific physical activity outcomes used in this study were determined from formative research with the target population. The most commonly reported positive (weight loss, improved fitness, more energy, less stress, improved mental well-being) and negative outcomes (injury, lose time to do other things) were included. Negative outcome expectancies were included because expectations are thought to be better predicted when both positive and negative outcomes are considered [41]. Our previous trial [26] and others [42] have demonstrated that the measure was sensitive to change in a physical activity intervention among postnatal women. The scale has acceptable internal consistency (Cronbachs α = 0.72) [26]. *Goal Setting Skills* are measured using the 10‒item Exercise Goal-setting Scale (EGS)[43]. This scale has good test retest reliability (r = 0.87) over an 8‒week period [43]. The EGS items assesses setting goals (e.g., I often set exercise goals), self-monitoring (e.g., I usually keep track of my progress in meeting my goals) and problem solving (e.g., If I do not reach my goals, I analyse what went wrong). Each item is measured on a 5-point Likert scale, but following our formative research with 12 postnatal women the original anchors (‘does not describe’ to ‘describes completely’) were found to be difficult to interpret so we adapted the EGS anchors to 1 ‘strongly disagree’ to 5 ‘strongly agree’. The adapted version of EGS had good internal consistency (Cronbachs α = 0.84) [26], similar to that of the original scale (r = 0.89)[43]. *Physical activity social support* from the participant’s partner (husband or defacto) and from their family or friends is assessed on a 5-point Likert scale using the Social Support for Exercise Scale [44]. Five items, including an additional one (‘offered to mind the kids so I could be more physically active’) are assessed on a scale from 1 ‘never’ to 5 ‘very often’. The original scale has good test-retest reliability (r = 0.55–0.79)[44], and this slightly modified version has demonstrated good internal consistency (Cronbachs α = 0.90) [26] and sensitivity to change among women with young children [10,26]. At T2 and T3 we included five additional items to specifically assess the support that participants received from their nominated MobileMums support person. *Perceived Environmental Opportunity for Exercise:* was measured using 12 items designed and implemented by Hoehner and colleagues [45]. These items were derived from a review of three commonly used questionnaires to assess environmental impact on physical activity participation [46], and are assessed on a five point Likert scale from 1 ‘strongly disagree’ to 5 ‘strongly agree’. Based on our formative research we added two additional items to the scale (‘There are footpaths wide enough to fit prams in my neighbourhood’; ‘Unattended dogs make it unsafe to walk in my neighbourhood’). The adapted scale has an acceptable internal consistency (Cronbachs α = 0.75) [26].

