### Sample size

Our sample size was based on the clinically meaningful increase in physical activity (assessed by the AWAS) observed in our pilot study (40 minutes/week) [27]. We chose to base the sample size on self-report physical activity data, not the objective accelerometer data, because our pilot data suggested the AWAS was likely to produce the higher sample size estimate due to larger variance. Using the variance observed in the self-report data of 102 minutes/week [27], and assuming 80% power and two-sided significance of 5% we needed 102 women per group. Estimating a 25% dropout, this figure was inflated to 128 per group, or 256 total.

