### Data analyses

Data analyses will follow intention-to-treat principles [28], so all participants will be analysed according to their randomised group regardless of whether they complied with the program or not. Missing physical activity data will be imputed using a model that accounts for the often skewed distribution of physical activity. Missing data will be imputed using a regression model based on time and a subject’s previous responses using a random intercept. To account for the uncertainty in imputing missing data the analyses will use multiple imputation using the WinBUGS software. Statistical significance will be set to 5% and 95% confidence intervals will be given for all results.

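### Mediation (RQ4) is tested only with the Sobel normal-theory test, which at about 200 women gives lopsided 95% limits and, unless the paths are large, loses power

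*Protocol article*

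**What the plan says.** The Mediator analysis section of the protocol article fixes the method: "Potential mediation will be explored using a simple product-of-coefficient approach using Sobel tests". The test asks whether the indirect effect "is significantly different from zero". No bootstrap, Monte Carlo or distribution-of-the-product interval is mentioned. The same section concedes that "this trial was not powered to detect mediation and this will be an exploratory analysis".

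Three other places bear on the point:

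- Theoretical mediators: "the following five constructs are being evaluated as potential mediators via the self-administered questionnaire at each data collection point".
- Data analyses: "Statistical significance will be set to 5% and 95% confidence intervals will be given for all results". This covers the mediated effects too.
- Background and Discussion: mediation is one of five numbered research questions (RQ4), and the Discussion expects the trial to inform the relative contributions of the theoretical constructs.

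The article gives no expected path coefficients and no power for the mediation test.

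**The concern.** The Sobel test divides the product of two estimated coefficients by a first-order standard error and refers the ratio to a normal distribution. Unless at least one path is large relative to its standard error, the product is skewed. The standard error also grows with the estimated coefficients, so low estimates come with short intervals. Two faults follow: a symmetric interval that misses far more often on one side than on the other, and a test that rejects too rarely.

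RQ4 is at stake. A construct that does carry part of the effect may be reported as not mediating, with limits that sit too low. An analysis that admits low power has particular reason to avoid a test that gives more of it away.

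**Working it through.** **Inputs from the article.** Two-sided 5% and 95% intervals (Data analyses). The sample size statement reads: "assuming 80% power and two-sided significance of 5% we needed 102 women per group". The difference is 40 minutes/week and the figure of 102 minutes/week, which the text calls a variance, works only as an SD.

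**The plan's own figure.** n = 2 × (1.96 + 0.8416)² × 102²/40² = 2 × 7.849 × 6.5025 = 102.07 per group. That is 103 when rounded up, against 102 stated, so the figure reproduces. It concerns the main outcome; there is no mediation figure to reproduce. Total sizes examined: 204 (2 × 102), 192 (256 × 0.75) and 256.

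**Assumed, because the article gives none.** a is the difference between arms in the mediator, in residual SDs (0 to 0.8). b is the slope of the outcome on the mediator, adjusted for arm, with unit residual SD (0 to 0.39).

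**Hand check at N = 204, a = 0.4, b = 0.2.**

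- SE(a) = √(4/204) = 0.140, so z_a = 2.857. SE(b) ≈ 1/√204 = 0.070, so z_b = 2.857.
- Sobel: ab = 0.08; SE = √(0.4² × 0.070² + 0.2² × 0.140²) = 0.0396; z = 2.02. With two equal paths, each needs z > 1.96 × √2 = 2.77 before the Sobel test rejects.
- Requiring both paths to be significant (joint significance) needs only 1.96 on each. Power ≈ Φ(2.857 − 1.96)² = 0.815² = 0.66.
- Skewness of the product = 6·z_a·z_b/(z_a² + z_b² + 1)^1.5 = 6 × 8.16/17.32^1.5 = 48.96/72.1 = 0.68. A normal variable has 0.

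**Simulation.** 4,000 replicates per scenario, 1:1 arms, linear models, one mediator, complete data, one time point, normal errors. Power at N = 204:

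| a | b | Sobel | Monte Carlo interval | Joint significance | Loss vs Monte Carlo |
|---|---|---|---|---|---|
| 0.2 | 0.14 | 4.5% | 12.2% | 15.3% | 63% |
| 0.3 | 0.14 | 11.0% | 27.8% | 28.4% | 61% |
| 0.3 | 0.2 | 24.2% | 42.6% | 45.3% | 43% |
| 0.4 | 0.2 | 43.3% | 64.7% | 64.9% | 33% |
| 0.4 | 0.3 | 70.0% | 80.2% | 80.2% | 13% |
| 0.5 | 0.3 | 87.6% | 94.4% | 93.8% | 7% |
| 0.5 | 0.39 | 92.4% | 94.6% | 94.4% | 2% |
| 0.8 | 0.39 | 100% | 100% | 100% | 0% |

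Loss is 1 − Sobel/Monte Carlo. In the first row the loss against joint significance is 1 − 4.5/15.3 = 71%. At a = 0.4, b = 0.2 the loss against the Monte Carlo interval is 35% at N = 192 and 20% at N = 256.

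**Interval balance at a = 0.4, b = 0.2.** At N = 204 the Sobel interval lies wholly below the truth in 7.8% of replicates and wholly above it in 0.6%, so coverage is 100 − 8.4 = 91.6%. The Monte Carlo interval misses 3.6% and 1.3%. The Sobel figures are 7.6% and 0.6% at N = 192, and 5.8% and 1.0% at N = 256.

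**Rejection when there is no mediation (nominal 5%).**

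- a = 0.4, b = 0, N = 192: Sobel 0.8% to 1.0% over three runs of 3,000 to 6,000 replicates; Monte Carlo 3.7% to 3.8% in two of them.
- a = 0, b about 0.4: Sobel 3.4% (b = 0.39, N = 204) and 3.5% (b = 0.4, N = 192); Monte Carlo 5.6% at b = 0.39. The simulation standard error is √(0.05 × 0.95/4000) = 0.34 points, so 5.6% is within two standard errors of 5%.
- a = b = 0, N = 204: Sobel about 0%, Monte Carlo 0.1%, joint significance 0.2%. Every method is conservative here.

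**The case against.** The strongest defence is that the article does not oversell this analysis. It calls mediation exploratory and unpowered and lists it among the secondary outcomes; no efficacy or cost-effectiveness conclusion depends on it. The Sobel test errs towards missing mediators rather than claiming false ones, which has some appeal with five constructs and no stated multiplicity adjustment. This limits the weight of the point. It does not justify the choice of test: low power argues against a conservative test, and the exploratory label does not correct limits that are misplaced.

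Several stronger readings are tempting, and the documents do not support them:

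- **That the test costs a fixed third of the power.** One third belongs to mid-sized paths such as a = 0.4, b = 0.2 at about 200 women. The article gives no path sizes.
- **That the true error rate is near 1%.** That holds at a = 0.4, b = 0. Elsewhere under the null it runs from 0% to about 3.5%, and the alternatives also fall far below 5% when both paths are zero.
- **That Sobel is the least powerful standard test.** Against a causal-steps test (total effect and both paths significant) at a = 0.4, b = 0.2 and N = 192, Sobel has 40% power against 5% with no direct effect, but 40% against 46% with a direct effect of 0.3 SD.
- **That the change has no downside.** The planned analysis uses multiple imputation, and a bootstrap has to be combined with it deliberately.

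It is also fair to object that the simulations leave out repeated measures, imputation and the skewed activity data that the article expects. One run with exponential outcome residuals at N = 192 kept the gap at a = 0.4, b = 0.2 (40% against 57%), but the exact figures may not carry over.

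**Conclusion.** The point stands as a modest but real flaw in the method fixed for RQ4. At about 200 women, under assumed paths a = 0.4 and b = 0.2, the Sobel interval misses on one side about 7-8% of the time and on the other under 1%. The relative power loss depends on path sizes that the documents do not give: near 0% for large paths, about one third at a = 0.4, b = 0.2, and about 60-70% for small paths (63% against the Monte Carlo interval and 71% against joint significance in the smallest case run). Null rejection is about 1% at a = 0.4, b = 0 and about 3.5% at a = 0, b = 0.4. These figures assume one mediator, one time point, complete data and linear models. A reader might infer that the trial's main result is in doubt. It is not, because the analysis of physical activity does not use this test.

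**What to change.** Keep the product-of-coefficients estimate and the exploratory label, and replace the Sobel test with one of the following:

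- **Monte Carlo (distribution-of-the-product) 95% interval.** Pool each path estimate and its standard error over the imputed data sets, draw both coefficients from their estimated sampling distributions, multiply them, and take the 2.5th and 97.5th percentiles. This is the simpler option with multiple imputation.
- **Percentile bootstrap.** Resample women, keeping all of a woman's assessments together, and state in advance how resampling and imputation are nested.

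Report estimates and intervals for all five constructs, and do not read an interval that includes zero as evidence that a construct plays no part. Record the change before the mediation results are seen.

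The change needs no participants or data. It costs some analysis work, mainly for the bootstrap, and a per-test false-positive rate that moves up towards 5%. In the a = 0.4, b = 0 case the rate goes from 1.0% to 3.8%, which over five such constructs adds 5 × 0.028 = 0.14 expected false positives. With the exploratory label kept, that is acceptable.

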### Moderator analysis

Exploratory analysis of potential moderators will determine whether intervention effects differ across demographic (e.g., age, gender) and health-related (e.g., BMI, SF-12) characteristics. This analysis will be performed by considering the statistical significance of an interaction between a potential moderator and the intervention as part of the generalised estimating equations model.

## Discussion

This paper describes the methods for evaluating the improved version of the MobileMums program in a large scale community-based randomised controlled trial. The results of this trial will address multiple indicators of program evaluation including efficacy, feasibility, acceptability, cost-effectiveness, mediation and moderation. The results will advance both the science and practice of physical activity interventions for women with young children.

The evidence base for physical activity interventions among women with young children is only starting to include evaluation of mediated (non face-to-face) mechanisms of program delivery [23,24], this is despite the need for highly accessible, flexible program delivery in this population with high caregiving demands. This trial will be the first (other than our pilot evaluation of MobileMums [27]) to evaluate a text message-delivered physical activity intervention for women with young children, and one of the first to evaluate a program delivered primarily by a mediated mechanism for this target group. Results of this trial will also contribute to the evidence for the application of Social Cognitive Theory in interventions to change physical activity and the relative contributions of the theoretical constructs as mediators of change.

Importantly, this trial will provide more valid evidence of the impact of MobileMums on overall physical activity by using objective physical activity measures from an adequately powered sample and assessing maintenance of behaviour change beyond the period of direct program delivery. Assessing the maintenance of behaviour change following an intervention is not common in physical activity trials in general [51] and is very rare within the evidence targeting women with young children. Another strength of this trial is the evaluation of cost-effectiveness of the MobileMums program. Cost reduction for program delivery is one of the key drivers for text message-delivered programs, but there is limited cost-effectiveness evidence to support this rationale.

This thorough evaluation will inform whether further translation of the MobileMums program beyond researcher-administration into community-based practice is warranted. The study investigators are conducting this trial within the context of an existing research-health delivery partnership and thus have the potential to rapidly facilitate the research findings into practice within the target community. We anticipate the findings of this trial will have impact on the practice of physical activity promotion for women with young children within our partnership region. Collectively, the evidence generated by this trial can inform physical activity promotion efforts for women with young children and other populations with accessibility to text messaging interventions, and advance the broader literature for physical activity behaviour change, application of Social Cognitive Theory, and delivery of health behaviour change programs via text messaging.

## Abbreviations

AWAS: Australian women’s activity survey; RQ: Research question.
